### Quality of life

All patients are asked to fill out questionnaires preoperatively, at 6 months and at 12 months after discharge from the hospital. The questionnaire has been constructed using previously used questions [28] that have been developed through a process of in-depth qualitative interviews and content validated by an expert panel consisting of colorectal surgeons, stoma care nurses and nurses specialised in surgery. The questionnaire was face-to-face validated by patients with a surgical procedure including a colostomy as well as patients with an existing colostomy using the validation methods described previously for a questionnaire for prostate cancer patients (26).

### Health economic evaluation

A health economic analysis will be performed based on the information collected in the CRF together with information from the hospital registries, based on the model presented by Bjöholt *et al.*[29]. The model will be used in combination with sensitivity calculations.

### Data collecting and monitoring

An operative CRF including reasons for surgery, planned operation and patient data, together with measurements from the surgical procedure is filled in for the operation (by the surgeon). For the hospitalisation period a nurse at the ward will complete a CRF, and for each follow-up visit a surgeon and a nurse will complete a CRF.

The postoperative questionnaires will be given to the patients by the stoma therapist. All data will be kept within University of Gothenburg and Sahlgrenska University Hospital systems using inherent security systems. A logistic database with complete patient ID will be used and kept within a separate IT system from the result database with all study information. Security measures will include one to maximum two users of this database, with unique usernames and personal login, as well as automatic throw-out. The questionnaires filled out by the patients are returned to the trial coordinating centre, SSORG, at Sahlgrenska University Hospital. The finalised database based on trial number and without patient ID, will be kept within another IT system than the logistic database.

### Statistical analysis

The Swedish trial on the effect of prophylactic net placement has reported 50% incidence of parastomal hernia without mesh [14]. Our own data on abdominoperineal excision from Sahlgrenska University Hospital indicate an incidence of 25% [28]. The power calculation based on available information has used the hypothesis that the cruciate incisional stoma formation, performed as described here, should result in parastomal hernia incidence of 30% and the circular incision or prophylactic mesh reinforcement could reduce this incidence to 10% each. An 80% power and a 5% level of significance with a two-sided alternative hypothesis would require 62 patients per group using a chi-square test. Expecting 20% drop-outs, 80 patients will be recruited in each group.

The primary analysis will be based on the full analysis set. This analysis set is designed to be consistent with recommendations set forth in International Conference on Harmonisation (ICH) guidance document E9: Statistical Principles for Clinical Trials, and is intended to adhere as closely as practically possible to the intention-to-treat (ITT) principle. The full analysis set will consist of all randomised patients who had surgery and who contributed with any follow-up data.

Patients will be analysed according to randomised procedure. A sensitivity analysis evaluating the actual procedure will be made for the most important outcomes.

All hypothesis testing will be conducted using two-sided tests, and P values ≤ 0.05 after rounding will be considered statistically significant. A pair-wise comparison between the experimental arms and the control arm will be performed and the significance level will be corrected using the Bonferroni-Holm method. Event-type variables (yes or no) will be compared between randomised procedures using chi-square tests, and relative risks and risk differences will be estimated. Where appropriate, the time to event will be described using Kaplan-Meier plots. The number of events of a certain type (for example, number of complications or re-operations) will be analysed using Poisson regression with randomised procedure as a factor and time under observation as an offset variable.

Total length of hospital stay will be compared between groups using Wilcoxon’s rank-sum test. Sub-group analyses specifically looking at the following groups of patients will be performed:

a) BMI >30 kg/m2

b) Immunosuppression

Sensitivity analyses will be performed for the primary variable and selected secondary variables, as deemed appropriate, where groups are compared pair-wise utilising only data from centres where both treatments were allocated.

Exploratory analyses (such as logistic regression) may be performed to investigate the influence of background factors (patient characteristics, perioperative factors) on outcomes.

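### Significance is judged on rounded p-values, so results slightly above the 5% level can be declared significant, and how rounding acts on the Holm steps is undefined

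*Protocol article*

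**What the plan says.** Everything relevant is in the Statistical analysis section of the protocol article.

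- Scope of the rule: "All hypothesis testing will be conducted using two-sided tests". The sentence goes on to the threshold: "P values ≤ 0.05 after rounding will be considered statistically significant". No number of decimals is given.
- Multiplicity, in the next sentence: "A pair-wise comparison between the experimental arms and the control arm will be performed", and "the significance level will be corrected using the Bonferroni-Holm method". There are two such comparisons, circular versus cruciate incision and mesh versus cruciate incision.
- Planned level: "An 80% power and a 5% level of significance with a two-sided alternative hypothesis would require 62 patients per group using a chi-square test". The assumed hernia incidence is 30% in the control arm, and either experimental technique "could reduce this incidence to 10% each". Then: "Expecting 20% drop-outs, 80 patients will be recruited in each group".

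The text does not say whether rounding is applied to raw or to Holm-adjusted p-values, or how it acts on a corrected level of 0.025.

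**The concern.** Rounding belongs to the display of a result. Once it is part of the decision rule, it moves the threshold. A p-value of 0.054 shown to two decimals reads 0.05 and counts as significant under this rule, although it exceeds the level at which the trial was planned. For an uncorrected 0.05 threshold, rounding can change a verdict in one direction only, towards significance.

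The rule covers all tests and so includes the primary endpoint. It is not a detail left open for a later analysis plan: the article states a threshold, and at any finite number of decimals that threshold lies above 5%. A later document that fixed the decimals would limit the excess but not remove it.

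Two things are at stake: the claimed 5% type I error, and a clear verdict if a primary comparison turns out borderline.

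**Working it through.** **Inputs from the article.** Two-sided 5% level, 80% power, 30% versus 10%, 62 per group, 20% drop-out, 80 recruited per group, two comparisons with control under Holm. **Assumption:** rounding to two or three decimals, since the article gives neither.

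**1. The plan's own figure.** Chi-square test without continuity correction, mean proportion 0.20:

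n = [1.960 × √(2 × 0.20 × 0.80) + 0.842 × √(0.30 × 0.70 + 0.10 × 0.90)]² / 0.20² = (1.109 + 0.461)² / 0.04 ≈ 61.6, so 62 per group.

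This reproduces. Drop-out: 62 / 0.8 = 77.5, so 78, which the plan takes to 80. Of 80 recruited, 80 × 0.8 = 64 remain evaluable. The calculation uses an unrounded 5% level.

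**2. Threshold implied by rounding, single test.**

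- Two decimals: every p below 0.055 becomes 0.05 or less. The level is just under 5.5% and the critical z is 1.919 instead of 1.960.
- Three decimals: every p below 0.0505 becomes 0.050 or less. The level is 5.05%.

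Normal-approximation power at 62 per group is 80.3% at 0.05 and 81.4% at 0.055, so the rule gives about one point of power in exchange for the looser level.

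**3. Exact size of one chi-square test, by enumeration, 64 per arm.**

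| True rate in both arms | p ≤ 0.05 | p < 0.0505 | p < 0.055 |
|---|---|---|---|
| 10% | 5.08% | 5.08% | 6.08% |
| 20% | 4.84% | 4.84% | 5.57% |
| 30% | 5.11% | 5.11% | 5.52% |

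At 62 per arm and a 30% rate, the size is 4.97% at p ≤ 0.05 and 5.71% at p < 0.055. The excess over nominal in the 10% row is partly discreteness of the test, which is already above 5% without rounding.

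**4. Holm with two comparisons.** Unrounded, the smaller p is compared with 0.025 and, if it passes, the larger with 0.05. The first-step threshold depends on the reading:

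- *Adjusted p-values rounded to two decimals.* The smaller p is doubled and passes if the result is below 0.055, so the first step is 0.055 / 2 = 0.0275. The second step is 0.055.
- *Raw p-values rounded to two decimals, compared with 0.025.* A p of 0.024 becomes 0.02 and passes; a p of 0.026 becomes 0.03 and fails. The first step stays at 0.025. The second step is 0.055.
- *Three decimals.* The first step is 0.0505 / 2 = 0.02525 (adjusted) or 0.0255 (raw). The second step is 0.0505.

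Familywise error with both nulls true, for two z-tests sharing a control (correlation 0.5), by simulation:

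| First-step threshold | Familywise error |
|---|---|
| 0.025 | 4.64% |
| 0.02525 | 4.69% |
| 0.0255 | 4.73% |
| 0.0275 | 5.09% |

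With chi-square tests at 64 per arm, a first step of 0.0275 gives 5.3%, 4.9% and 5.2% at true rates of 10%, 20% and 30%. When only one null is true and the other comparison is almost certain to be rejected, the true null is in effect tested at the second step, so the nominal error approaches 5.5% at two decimals.

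**5. Tables that show the dependence on format (64 per arm, Pearson chi-square).**

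- 14/64 versus 6/64: p = 0.0515. 18/64 versus 9/64: p = 0.0512. Where the 0.05 threshold applies, both are significant at two decimals (0.05) and not at three (0.051).
- 14/64 versus 5/64 at the first Holm step: raw p = 0.02526, adjusted p = 0.0505. It passes if the adjusted value is rounded to two decimals (0.05). It fails if the raw value is rounded to two decimals and compared with 0.025 (0.03), and it fails at three decimals on either reading (adjusted 0.051; raw 0.025 is the one exception, since 0.025 does not exceed 0.025).

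**The case against.** The strongest reply is that this is loose wording with little effect, and on size that stands. The excess is at most about 0.5 percentage points of nominal level at two decimals and 0.05 at three. At three decimals the exact size at 64 per arm does not change to the precision shown. Under the design alternative with 64 per arm, p falls between 0.05 and 0.055 with a probability of only about 1.7%, and between 0.025 and 0.0275 with about 0.9%.

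Three stronger readings are tempting, and the article supports none of them.

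- *The rounding rule contradicts or overrides Holm.* A flat rounded 0.05 applied to both comparisons would give a familywise error of about 9.9%. But the Holm sentence follows directly and modifies the level for the comparisons with control, so the two can be read together as Holm-adjusted p ≤ 0.05. What remains is an undefined interaction, and one plausible reading leaves the first step uninflated.
- *The primary analysis runs at 5.5% to 6.1%.* Those figures belong to one uncorrected comparison at two decimals. With Holm and both nulls true, familywise error stays near 5%.
- *The precision can be picked once the results are known.* The rule is stated in advance for every test, and nothing in the article suggests a data-dependent choice. The absence of a stated precision is a gap, not evidence of intent.

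It can also be said that the number of decimals is commonly left to the statistical analysis plan. That is fair for the precision. It does not rescue the rule, which accepts p-values above 0.05 at whatever precision is chosen.

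**Conclusion.** The point holds as a small defect in a stated decision rule. Judging significance after rounding admits p-values above the 5% level on which the sample size rests: up to just under 0.055 if two decimals are used, and up to just under 0.0505 if three are. Those levels apply to a single test and to the second Holm step.

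For the primary comparisons, the consequence depends on a reading that the article does not settle. In the least favourable one (adjusted p-values, two decimals), familywise error is about 5% with both nulls true and up to about 5.5% nominally with only one true, so Holm's 5% guarantee is no longer assured. With raw p-values rounded to two decimals, only the second step is loosened.

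These sizes rest on the assumed number of decimals and, for the exact figures, on about 64 evaluable patients per arm and the uncorrected chi-square test. Only borderline results are affected. The 62 and 80 per group are not in question here.

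**What to change.** Replace the rounding clause with wording such as: *Decisions are based on unrounded p-values. For the two comparisons with the control arm, unrounded Holm-adjusted p-values are compared with 0.05. Rounding is used for display only.*

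This settles both the threshold and its relation to the Holm steps. It needs no new data, leaves the planned 62 evaluable and 80 recruited per group as they are, and costs one short edit, best made before the outcome data are analysed.

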## Background

Colostomy formation has been a standard surgical procedure for more than 100 years. A well-functioning colostomy may not negatively affect the patient’s quality of life (QoL) [1]; however, this can only be said if the stoma is well functioning and if complications are kept to a minimum. The complication rates after stoma formation are considerable, with figures of 21-70% [2,3], and studies have shown that adequate stoma height, type of stoma, body mass index (BMI), emergency surgery and gender may be of importance in reducing the risk of complications in both the short- and long-term perspectives [4-6].

The surgical technique of stoma formation is only partly evidence based. There are few studies focused on technical details about stoma construction and their future impact on stoma function. One study has attempted to standardise the skin incision to two-thirds of the width of the bowel [7], although the actual impact of this on the functional outcome of the stoma function was not presented. In the surgical literature a cruciate incision in the fascia and extraction of the bowel through a hole sufficient in size is a standard description of the surgical technique [8]. In clinical practice the sufficient size of the hole has often been equal to ‘two fingers-width’ , which is a fairly inexact measurement.

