### Randomisation

All participating patients give written informed consent. After inclusion no changes are made in the planning for the operation. The patient will be randomised to one of the three groups of intervention during surgery in the operating theatre directly prior to the stoma formation (Figure 1). Randomisation will be performed by blocks of closed envelope systems in each participating hospital. It will be balanced and stratified by hospital. Laparoscopic as well as open procedures will be included and, although not stratified by open or laparoscopic procedures, their use will be noted in the CRF.

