**Figure 1 F1:**
[figure not shown]
Consort diagram for the Stoma-Const trial.

Including hospitals may choose to randomise between all three techniques or two of them. This decision is made before the hospital enters the study. The blocks will be set up according to this system, and the total number of 80 patients in each group will be managed through this system.

When patients are not subject to the treatment modality as randomised, data will be analysed on an ‘intention-to-treat basis’ (once randomised, patients will not be excluded or change groups because of conversion or type of surgery). Patients who do not consent to participation or are excluded will be treated by cross incision in the fascia as the usual routine.

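### Randomisation is stratified by hospital and hospitals may run only two of the three arms, but the primary test and effect estimates ignore hospital, so their standard error is wrong in a direction that depends on the layout

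*Protocol article*

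**What the plan says.** All locations are in the protocol article.

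- **Randomisation.** Closed envelopes in blocks are used at each hospital: "It will be balanced and stratified by hospital". The text after Figure 1 adds: "Including hospitals may choose to randomise between all three techniques or two of them". Each hospital decides before it enters the study.
- **Statistical analysis, test.** "Event-type variables (yes or no) will be compared between randomised procedures using chi-square tests, and relative risks and risk differences will be estimated". This covers the primary endpoint, which is a yes/no variable. Each experimental arm is compared with the cruciate arm, with Bonferroni-Holm correction. No stratum or covariate is named for the test, the relative risk or the risk difference.
- **Statistical analysis, sample size.** The cruciate stoma "should result in parastomal hernia incidence of 30" per cent, and either alternative "could reduce this incidence to 10% each". Then: "An 80% power and a 5% level of significance with a two-sided alternative hypothesis would require 62 patients per group using a chi-square test". Recruitment is 80 per group to allow for 20% drop-out.
- **Statistical analysis, later paragraphs.** A sensitivity analysis repeats the pair-wise comparisons using only centres that allocated both treatments. "Exploratory analyses (such as logistic regression) may be performed to investigate the influence of background factors"; hospital is not named among those factors.

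**The concern.** Hospital is the only stratification factor, and the stated primary analysis leaves it out. Two features of the design make this matter, and they act in opposite directions.

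First, blocking within hospital balances the compared arms inside each hospital that runs both. Differences between hospitals then cancel from the observed risk difference, but the pooled standard error still includes them. The test becomes conservative and some power is lost.

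Second, a hospital running only two arms may supply one side of a comparison and not the other. For circular versus cruciate, a hospital running cruciate and mesh contributes controls only, and one running circular and mesh contributes circular patients only. Pooling compares these patients across hospitals, which randomisation does not protect. Hospital differences then add to the real variability of the estimate, and the pooled standard error does not reflect this. False-positive findings become too frequent.

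**Working it through.** **1. The plan's own figure.** With p1 = 0.30, p2 = 0.10 and mean 0.20:

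n = [1.96 × √(2 × 0.20 × 0.80) + 0.8416 × √(0.30 × 0.70 + 0.10 × 0.90)]² / 0.20² = (1.109 + 0.461)² / 0.04 = 61.6, so 62 per group (power 80.3%).

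62 / 0.8 = 77.5, so 78, which the plan rounds up to 80. The sizing therefore agrees with an unstratified chi-square test. With 20% drop-out, 80 × 0.8 = 64 are analysed per arm.

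**2. Tests compared.**

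- Pooled: z = (p̂C − p̂E) / √[p̄(1 − p̄)(1/nC + 1/nE)].
- Hospital-stratified Cochran-Mantel-Haenszel (CMH): z = Σ(xh − nCh·mh/nh) / √Σ[nCh·nEh·mh(nh − mh) / (nh²(nh − 1))], summed over hospitals h that have both arms. Here xh is control events, mh all events and nh all patients.

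**3. Assumptions not in the protocol.** There are 8 hospitals with normally distributed hospital effects on the log-odds scale, SD 0, 0.5, 0.8 or 1.2. The null rate is 20%; the alternative is 30% versus 10% overall. Each setting has 40,000 runs (Monte Carlo error about 0.1 point for type I error and 0.2 for power).

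**4. Every hospital runs both arms (8 hospitals, 8 per arm each), two-sided 5%.**

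| SD | Type I, pooled | Type I, CMH | Power, pooled | Power, CMH |
|---|---|---|---|---|
| 0 | 4.7% | 4.9% | 82.2% | 82.5% |
| 0.5 | 4.5% | 4.9% | 82.4% | 83.3% |
| 0.8 | 4.1% | 5.0% | 83.1% | 85.0% |
| 1.2 | 3.3% | 5.0% | 83.5% | 87.4% |

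The loss is 0 to 4 points when the overall rates are held at 30% and 10%. If the within-hospital odds ratio is held instead, at (0.10/0.90)/(0.30/0.70) = 0.26, the loss reaches about 6 points at SD 1.2 and is still about 1 point at SD 0.5.

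The mechanism shows at SD 1.2. The true SD of the risk difference is 0.0643 and the average estimated standard error is 0.0689. The effective cut-off is about 1.96 × 0.0689/0.0643 = 2.10, a two-sided tail of about 3.6%, close to the simulated 3.3%.

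**5. Some hospitals lack a compared arm.**

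- One unshared hospital per side (6 × 9 + 10 = 64 per arm): pooled type I error is 5.2%, 5.7% and 6.5% for SD 0.5, 0.8 and 1.2.
- Two unshared hospitals per side (4 × 8 + 2 × 16 = 64 per arm): pooled type I error is 8.1%, 12.7% and 19.2%; a repeat put the upper end near 20%. CMH stays at 4.8% to 5.1%.

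At SD 0.8 with two per side, the true SD is 0.0906 and the estimated standard error 0.0692. The effective cut-off is about 1.96 × 0.0692/0.0906 = 1.50, a tail of about 13%, in line with 12.7%.

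In that layout CMH power is only 53% to 59% across SD 0 to 1.2 (about 48% to 53% with the odds ratio held), against 82% falling to 74% for the pooled test, because unshared hospitals drop out of CMH.

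**6. A joint three-arm model.** Assumed layout: four three-arm hospitals plus one hospital for each two-arm pair, 64 per arm, 4,000 runs, 5% level, logistic regression with procedure and hospital.

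| SD | Type I, pooled | Type I, joint | Power, pooled | Power, joint | Power, CMH |
|---|---|---|---|---|---|
| 0.5 | 6.8% | 5.1% | 79.5% | 75.6% | 71.3% |
| 0.8 | 7.7% | 4.5% | 80.0% | 77.8% | 73.8% |
| 1.2 | 12.0% | 5.4% | 77.6% | 78.6% | 75.9% |

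The joint model holds the type I error and recovers part of the power that CMH loses, because two-arm hospitals inform a comparison indirectly through the third arm.

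**The case against.** The strongest reply has four parts.

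*The protocol already deals with centre.* It plans a sensitivity analysis limited to centres that allocated both treatments. This does remove the non-randomised part of the comparison. But it selects centres without stratifying by them, and it is not the primary result. A false-positive primary finding would stand beside it with no rule for which prevails.

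*The effect may be negligible.* If hospitals have the same hernia rate, nothing is lost in either direction. If all hospitals run all arms, type I error stays at or below about 5%. Both statements are correct. The protocol gives neither the number of hospitals, nor their variation, nor how many chose two arms.

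*Stratifying can cost power.* This is also correct. A pair-wise CMH test would lose a great deal if many hospitals lacked a compared arm, so it is not a general remedy. The pooled test's apparent advantage comes partly from comparing patients across hospitals without randomisation.

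*The analysis plan may settle it.* It may, but the protocol does not leave the method open: it names the test and the estimates.

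A reader might also infer that the planned test errs only on the safe side. The two-arm option rules that out. A reader might infer that leaving out BMI is part of the same error. It is not: BMI is not a stratification factor, and the Background says only that "body mass index (BMI), emergency surgery and gender may be of importance in reducing the risk of complications", which concerns stoma complications generally.

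**Conclusion.** The mismatch between design and primary analysis is real. Its consequence is conditional on hospitals differing in hernia rate, and its direction depends on which arms each hospital runs.

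- **All hospitals run both compared arms:** a mildly conservative test and a modest power loss, about 1 point at SD 0.5.
- **Some hospitals omit a compared arm:** inflated type I error, slight with one unshared hospital per side and serious with two. This is the more important reason to act.

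All sizes rest on 8 hospitals, 64 analysed per arm and an assumed SD range. The protocol does not support a claim that power is certainly lost, or that error is certainly inflated. The stated 62 per group is arithmetically right for the planned test at the full 5% level; the effect of the Holm correction on power is a separate matter.

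**What to change.** Make the primary analysis a single model of all three arms with procedure and hospital as factors, for example logistic regression. Derive standardised risk differences and relative risks from that model, and keep Holm for the two comparisons with the cruciate arm.

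- Use a hospital-stratified CMH test instead only if all or nearly all hospitals run both compared arms.
- Pool small hospitals only with others that have the same set of arms, by a rule fixed before the data are seen. Merging different sets of arms would bring back the non-randomised comparison.
- Keep the plain chi-square test and the planned shared-centre analysis as sensitivity analyses.
- BMI adjustment is optional.

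The cost is wording and a few lines of code, with no new data. The real downside is that hospitals lacking a compared arm contribute less information, so nominal power can fall below that of the pooled test: in the joint-model layout above, by about 4 points at SD 0.5 (79.5% to 75.6%) and 2 points at SD 0.8 (80.0% to 77.8%).

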### Endpoints

The primary endpoint is the presence of parastomal hernia as detected by clinical examination or CT scan at 12 months after surgery. A bulge in the vicinity of the stoma is not sufficient in this study to define a parastomal hernia. If there is any doubt in the clinical setting, the patients must be examined by a CT scan in a prone position. Secondary endpoints include: re-admission rate, postoperative complications (classified according to Clavien-Dindo [27]), stoma-related complications (registered in the case record form (CRF) at Stoma Care nurse follow-up), total length of hospital stay during 12 months, health-related quality of life and health economic analysis, re-operation rate, mortality within 30 days and 12 months of primary surgery. Re-admissions and re-operations as registered in the hospitals’ databases at 24 months to ascertain that possible long-term complications related to the stoma construction are identified.

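### Event counts are analysed by Poisson regression with no allowance for overdispersion, so standard errors are too small if patients differ in risk or have repeated events of the same type

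*Protocol article*

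**What the plan says.** The Statistical analysis section of the protocol article fixes the model for counts. Numbers of events of one type, with complications and re-operations given as examples, "will be analysed using Poisson regression with randomised procedure as a factor and time under observation as an offset variable". Procedure is the only factor in the model; observation time enters as an offset.

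The outcomes involved are secondary. The Endpoints section lists them: "Secondary endpoints include: re-admission rate, postoperative complications (classified according to Clavien-Dindo [27]), stoma-related complications", with re-operations later in the same list.

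The general testing rule is "All hypothesis testing will be conducted using two-sided tests, and P values ≤ 0.05 after rounding will be considered statistically significant". For the comparisons of each experimental arm with control, "the significance level will be corrected using the Bonferroni-Holm method".

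The article does not mention overdispersion, a scale parameter, robust standard errors, a negative binomial model or a check of the Poisson variance. Its planned sensitivity analyses deal with the procedure actually performed and with centres that allocated both treatments being compared. Neither bears on the variance of the counts.

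**The concern.** A Poisson model assumes that, given the covariates, variance equals mean. With procedure as the only factor, every other difference in risk between patients becomes extra variance, and so do repeats of the same event in one patient. The offset corrects for unequal follow-up, not for this.

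The article itself gives reason to expect differences in risk. Its Background names BMI, gender, stoma height and type of stoma as possible influences on complications. Eligibility is open to essentially any elective colostomy patient, with one exclusion criterion. Subgroup analyses are planned for high BMI and immunosuppression.

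At stake is the reading of the safety comparisons. The Background says that reluctance to use a prophylactic mesh rests mainly on the possible risk of infection. If complication counts are overdispersed and the standard errors are model-based, a few patients with many events in one arm could produce a significant difference by chance, in either direction.

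**Working it through.** **The plan's own figure.** The article states no figure for the count analyses. Its one sample-size figure is for the primary endpoint: 30% in the control arm, which the new techniques "could reduce this incidence to 10% each", and "An 80% power and a 5% level of significance with a two-sided alternative hypothesis would require 62 patients per group using a chi-square test".

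- n = [1.96 × √(2 × 0.20 × 0.80) + 0.8416 × √(0.30 × 0.70 + 0.10 × 0.90)]² / 0.20² = (1.1087 + 0.4610)² / 0.04 = 61.6, so 62 per group, with power 0.803.
- Allowing for 20% drop-out, 62 / 0.80 = 77.5, so 78, against the 80 planned.

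The figure is reproduced. It rests on a yes/no outcome and a chi-square test, so nothing below changes it.

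**Inputs for the count analysis.** Two-sided testing at 5% comes from the article. The mean count and its variance do not. The complication figures of 21–70% in the Background are rates from other studies and give no variance of counts per patient. The variance-to-mean ratio φ is therefore assumed, starting at 1 (no overdispersion).

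**Formula.** If the true variance is φ times the mean, the model-based standard error is 1/√φ of the correct one, and intervals are too narrow by a factor √φ. The true two-sided error of a nominal 5% Wald test is 2 × [1 − Φ(1.96/√φ)].

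| φ (assumed) | √φ | Model SE as share of correct SE | 1.96/√φ | True error |
|---|---|---|---|---|
| 1.0 | 1.00 | 100% | 1.960 | 0.050 |
| 1.2 | 1.10 | 91% | 1.789 | 0.074 |
| 1.5 | 1.22 | 82% | 1.600 | 0.110 |
| 2.0 | 1.41 | 71% | 1.386 | 0.166 |
| 3.0 | 1.73 | 58% | 1.132 | 0.258 |

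**Simulation check.** Counts were drawn from a gamma-Poisson distribution with φ = 1 + kμ, where μ is the mean per patient and k the dispersion. Follow-up was equal, with 80 patients per arm, no true difference and 40,000 replicates.

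| φ | μ and k | Plain Poisson error | Robust (sandwich) error |
|---|---|---|---|
| 1.0 | 0.2 to 1.5; k = 0 | 0.044–0.049 | 0.048–0.053 |
| 1.2 | 0.2; 1 | 0.065 | 0.050 |
| 1.5 | 0.5; 1 and 1.0; 0.5 | 0.105–0.108 | 0.054–0.055 |
| 2.0 | 0.5; 2 and 1.0; 1 | 0.161–0.164 | 0.057–0.059 |
| 3.0 | 1.0; 2 | 0.252 | 0.059 |

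Over all scenarios tried (μ from 0.2 to 1.5, k from 0 to 3) at 80 per arm, plain Poisson ranged from about 0.044 to 0.40 and the robust version from 0.048 to 0.064.

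**How frequency matters.** Because φ = 1 + kμ, rare events stay near the Poisson variance. With k = 1, a mean of 0.2 events gives φ = 1.2 and an error of about 0.07; a mean of 1 gives φ = 2 and about 0.17.

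**Multiplicity.** With two comparisons against control, the first Holm step tests at 0.05/2 = 0.025, with critical value 2.241. The same formula, 2 × [1 − Φ(2.241/√φ)], gives 0.041, 0.067, 0.113 and 0.196 for φ = 1.2, 1.5, 2 and 3. The correction lowers the threshold, but each test still exceeds its nominal level.

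**The case against.** The strongest reply is that this is a journal article and the analysis plan is not shown. The article fixes a rate model with an offset, which the fix keeps. A Poisson model with a sandwich variance is still Poisson regression, and the unseen plan may already specify one. That possibility is real and limits how hard the point can be pressed. It does not remove it: the article names the family, the only factor and the offset, and followed as written with the usual model-based errors, the analysis fails whenever counts are overdispersed.

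Other limits stand in full:

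- A reader might infer that the intervals in this trial will be too narrow and the safety P values too small. The documents do not support that flat statement. They give no dispersion, and with φ between 1.0 and 1.2 the error is only 5% to 7%.
- A reader might also count a complication that leads to a re-operation as overdispersion. The plan models events of one type at a time, so such a link does not in itself inflate either count. Only repeats of the same type, or differences in risk between patients, do so.
- The article also compares yes/no event variables by chi-square test. A comparison of patients with any re-operation, for example, is unaffected by repeats within a patient and could expose an excess driven by a few people.

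**Conclusion.** The point holds in conditional form. The stated count model makes no allowance for overdispersion, and neither the Bonferroni-Holm correction nor the planned sensitivity analyses supply one. If counts of the same event type are overdispersed and model-based standard errors are used, a nominal 5% test has a true error of about 7% at φ = 1.2, 11% at 1.5, 17% at 2 and 26% at 3; at φ = 1 there is no error.

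These values of φ are assumptions, and the documents cannot say which applies. The low end is plausible for rare events such as re-operations. The higher values require frequent or strongly clustered events, as complications might be if they average about one per patient. The consequence is confined to secondary endpoints.

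**What to change.** Keep the Poisson rate model with the observation-time offset, and state that standard errors, intervals and tests use a robust (sandwich) variance. Negative binomial regression with the same offset is an acceptable alternative. One of the two should be named before results are seen, so that the variance method is not chosen from the data.

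The change takes one sentence in the analysis plan and one software option. The statistical cost is that intervals widen by √φ where counts are overdispersed: about 1.10 times at φ = 1.2, 1.22 at 1.5, 1.41 at 2 and 1.73 at 3. Where counts are not overdispersed they hardly change. In the simulations the robust test could run slightly above nominal (at most 0.064 at 80 per arm), far less than the inflation it removes. No change to recruitment or to the primary analysis is needed.
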